## Abstract

**Background:**

Treatment of pulmonary sarcoidosis is recommended in case of significant symptoms, impaired or deteriorating lung function. Evidence-based treatment recommendations are limited and largely based on expert opinion. Prednisone is currently the first-choice therapy and leads to short-term improvement of lung function. Unfortunately, prednisone often has side-effects and may be associated with impaired quality of life. Methotrexate is presently considered second-line therapy, and appears to have fewer side-effects.

**Objective:**

The primary objective of this trial is to investigate the effectiveness and tolerability of methotrexate as first-line therapy in patients with pulmonary sarcoidosis compared with prednisone. The primary endpoint of this study will be the change in hospital-measured Forced Vital Capacity (FVC) between baseline and 24 weeks. Secondary objectives are to gain more insights in response to therapy in individual patients by home spirometry and patient-reported outcomes. Blood biomarkers will be examined to find predictors of response to therapy, disease progression and chronicity, and to improve our understanding of the underlying disease mechanism.

**Methods/design:**

In this prospective, randomized, non-blinded, multi-center, non-inferiority trial, we plan to randomize 138 treatment-naïve patients with pulmonary sarcoidosis who are about to start treatment. Patients will be randomized in a 1:1 ratio to receive either prednisone or methotrexate in a predefined schedule for 24 weeks, after which they will be followed up in regular care for up to 2 years. Regular hospital visits will include pulmonary function assessment, completion of patient-reported outcomes, and blood withdrawal. Additionally, patients will be asked to perform weekly home spirometry, and record symptoms and side-effects via a home monitoring application for 24 weeks.

**Discussion:**

This study will be the first randomized controlled trial comparing first-line treatment of prednisone and methotrexate and provide valuable data on efficacy, safety, quality of life and biomarkers. If this study confirms the hypothesis that methotrexate is as effective as prednisone as first-line treatment for sarcoidosis but with fewer side-effects, this will lead to improvement in care and initiate a change in practice. Furthermore, insights into the immunological mechanisms underlying sarcoidosis pathology might reveal new therapeutic targets.

**Trial registration:**

The study was registered on the 19th of March 2020 in the International Clinical Trial Registry, www.clinicaltrials.gov; ID NCT04314193.

## Background

Sarcoidosis is a multisystem, granulomatous disorder of unknown cause, which most commonly affects the lungs. Patients often have organ-specific symptoms such as dyspnea and cough, but many patients also suffer from a wide range of other disabling, non-specific symptoms including fatigue, stress, anxiety, depression, small-fiber neuropathy, decreased exercise tolerance, cognitive impairment, and chronic pain [1, 2]. These symptoms have a major impact on quality of life (QoL) and social as well as work participation of sarcoidosis patients [1, 2]. Treatment of pulmonary sarcoidosis should be considered for patients with significant pulmonary symptoms and patients with an impaired or deteriorating lung function [3, 4]. The ATS/ERS/WASOG guideline, dating from 1999, recommends oral corticosteroids as the first-choice therapy for pulmonary sarcoidosis and this is also reflected in a recent Delphi consensus statement and current practice [5–7]. These recommendations are mainly based on expert opinion and limited evidence from observational studies. Both state that more research is needed to define the best treatment for patients with pulmonary sarcoidosis [5–7]. Although corticosteroid treatment leads to short-term improvement of pulmonary function, radiological improvement, and symptom reduction, previous studies have not conclusively demonstrated a beneficial effect in preventing disease progression in the long-term [3, 4, 7]. Corticosteroids can have debilitating side-effects, such as diabetes, osteoporosis, depression and weight gain [8–10]. Long-term use of corticosteroids is associated with impaired QoL [11]. Hence, there is a major need to find better treatment options for sarcoidosis with fewer side-effects and less impact on QoL.

Methotrexate is most used as second-line therapy, when prednisone is ineffective or not tolerated, and appears to have fewer side-effects [7, 12]. Even though methotrexate is sometimes used as first-line therapy in case of (relative) contra-indications for prednisone, no data on its effectiveness as first-line treatment for pulmonary sarcoidosis exist. A number of studies evaluated the efficacy of methotrexate as second-line treatment for sarcoidosis, and showed that methotrexate had a significant steroid-sparing effect and improved pulmonary function [13–16] . Most commonly reported side-effects in these studies were gastro-intestinal complaints, headache, general malaise and infections. These side-effects only led to treatment discontinuation in a minority of cases. Moreover, according to a sarcoidosis expert survey, methotrexate seems to be safe and well tolerated when used for a prolonged period of time [12].

Tailoring of existing therapies and development of new treatments is also hampered by the incomplete understanding of the pathobiology of sarcoidosis [17]. Biomarkers predictive of disease behavior and response to therapy are highly needed to avoid overtreatment with unnecessary side-effects in some patients and undertreatment with possible organ damage as a result in others. The ideal biomarker is highly sensitive, widely reproducible, rapidly available and low priced. Unfortunately, none of the currently used biomarkers in sarcoidosis care fulfills these criteria [18]. Available data indicate a role for specific T-cells, called Th17.1-cells, and cytokine expression in dendritic cells (DCs) in predicting disease course [19]. Furthermore, higher numbers of intermediate and non-classical monocytes at baseline also seem related to response to therapy in patients treated with infliximab [20] . Further advances in serum as well as cellular biomarker discovery can provide more insights into disease mechanisms, disease behavior, and response to therapy. Home monitoring of lung function and patient reported outcomes is a more clinical approach to assess response to treatment, as this will allow for more detailed information on treatment effect [8, 21]. Together, this will contribute to personalized treatment of sarcoidosis.

This paper describes the design of the PREDMETH study, which will evaluate the efficacy of methotrexate as first-line treatment for pulmonary sarcoidosis compared to prednisone, and aims to improve evidence-based treatment options and quality of life for patients with sarcoidosis.

## Methods/design

### Objectives and endpoints

The main objective of this study is to investigate the effectiveness and tolerability of methotrexate as first-line therapy in patients with pulmonary sarcoidosis compared with prednisone. The primary endpoint of this study is the change in hospital-measured Forced Vital Capacity (FVC) between baseline and 24 weeks. Secondary objectives are to gain more insights in response to therapy in individual patients by home spirometry and patient reported outcomes. Furthermore, we aim to also examine blood biomarkers of disease progression and chronicity, to assess whether response to therapy can be predicted in individual patients, and to gain more insights into the underlying disease mechanism and potential new targets for therapy. Table 1 shows the endpoints of the PREDMETH study.

**Table 1 Tab1:** Endpoints of the PREDMETH study listed as primary endpoint, secondary endpoints and explorative endpoints

Primary endpoint	
- Between-group difference in change in hospital-measured Forced Vital Capacity (FVC) % predicted between baseline and 24 weeks	
Secondary endpoints	
- Difference in change in FVC % predicted at 4, 16 weeks, 1 year and 2 years between prednisone and methotrexate group - Time to major pulmonary improvement measured by home-measured FVC, whereby major pulmonary improvement is defined as 80% of the maximum percent predicted FVC reached anywhere during the first 24 weeks of treatment - The percentage of patients with ≥5 and ≥ 10% improvement or decline in FVC at 4, 16 and 24 weeks - The percentage of patients with ≥10% improvement or decline in DLCO at 4, 16 and 24 weeks - Change over time in (Health-related) quality of life measured by King’s Sarcoidosis Questionnaire (KSQ), Global Rating of Change scale (GRoC), Chronic Respiratory Questionnaire (CRQ) and Euroqol-5D-5L questionnaire (EQ-5D-5L) at every clinical visit - Time to symptom improvement. Symptom scores measured by Visual Analogue Scales (VAS), Medical Research Council dyspnea scale (MRC) and Fatigue Assessment Scale (FAS) - Expectations with medication at baseline - Experiences and satisfaction with medication measured by the Patient Experience and Satisfaction with Medication Questionnaire (PESaM) - Number, severity and impact of side-effects compared between methotrexate and prednisone - Number of patients who discontinue/switch medication - Adherence to treatment schedule (% of patients that received at least 90% of the total cumulative dose after 24 weeks). - Correlation between angiotensin coverting enzyme (ACE), serum soluble interleukin-2 receptor (sIL-2R) and clinical parameters	
Explorative endpoints	
- Asses predictors of disease progression and response to therapy - Correlations between biomarker characteristics and clinical parameters - Change in biomarkers over time - Explore potential differences in distribution/phenotypes of monocytes, Th-cells, dendritic cells and new biomarkers identified using proteomics between patients during treatment with prednisone or methotrexate at all points	

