### Design and participants

The PREDMETH study is a prospective, randomized, non-blinded, multi-center, non-inferiority trial, designed to compare effectiveness and tolerability of methotrexate versus prednisone as first-line therapy for pulmonary sarcoidosis. The study is a joint design of clinicians, scientists and a patient expert panel. In this study, 18 centers in the Netherlands will participate. The study will randomize a total of 138 treatment-naïve adult sarcoidosis patients, about to start first-line therapy for a pulmonary indication.

Patients will be informed about the study by their treating physician. If patients are willing to participate, written informed consent will be obtained, and patients will be screened for eligibility. The in- and exclusion criteria are shown in Table 2. If eligible, patients will be randomized in a 1:1 ratio to receive either prednisone or methotrexate for 24 weeks, after which they will be followed up in regular care up to 2 years. For allocation of each subject to a treatment arm a centralized electronic randomization system will be used. Hospital visits will take place at 4, 16 and 24 weeks, and for long-term follow-up after 1 year and 2 years. Additionally, patients will be asked to perform weekly home spirometry and record symptoms and side-effects via a home monitoring application for 24 weeks.

**Table 2 Tab2:** Inclusion and exclusion criteria

Inclusion criteria	Exclusion criteria

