### Hospital visits

Baseline characteristics of patients, such as gender, age, self-reported ethnicity, smoking status, comorbidity, co-medication, date of sarcoidosis diagnosis, details of organ involvement, and if available details of x-ray and chest CT scan will be recorded. At every visit, a physical examination will be performed to record weight, height, waist circumference and blood pressure of the patients. In-hospital pulmonary function measurements will include FVC, Forced Expiratory Volume in 1 second (FEV1) and diffusion capacity of the lung for carbon monoxide (DLCOc). Furthermore, routine blood samples will be collected to assess blood count, kidney- and liver function. An additional sample of 80 ml blood will be taken for analysis of Angiotensin coverting enzyme (ACE), Serum soluble interleukin-2 receptor (sIL-2R), monocyte subsets, T-cells, dendritic cells, and proteomics biomarker discovery. Patients will also be asked to complete patient-reported outcome measures (PROMs) via a home monitoring app at every visit. The PROMs consist of the Fatigue Assessment Scale (FAS), the King’s Sarcoidosis Questionnaire (KSQ), Global Rating of Change Scale (GRoC), Chronic Respiratory Questionnaire (CRQ), Patient Experience and Satisfaction with Medication Questionnaire (PESaM) and Euroqol-5D-5L questionnaire (EQ-5D-5L). At follow-up visits all adverse events will be evaluated and recorded. Side-effects will be managed according to the discretion of the treating physician. Physicians can deviate from the treatment flowchart at any time, if the clinical situation demands so. The study design is shown in Table 3.

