### Home monitoring

For home monitoring of pulmonary function, symptoms and side-effects, a home monitoring application will be used, which has previously been developed together with sarcoidosis patients [21]. The application will be installed on a smartphone or tablet. In this CE-marked, secured application (Curavista, the Netherlands), patients will keep track of their own data, such as pulmonary function, side-effects and symptoms. A graphic overview of results is available, so patients can gain more insight in their disease course, an example is shown in Fig. 2. A handheld spirometer (Spirobank Smart, MIR, Italy) will be handed out to all patients. Patients will be instructed to undertake spirometry (three consecutive measurements) once a week at the same day, at approximately the same time to enhance compliance and reduce variability [23]. The best result of the day will be transmitted real-time to the patients’ personal platform and will be directly accessible for both patients and the study team. This will enable close monitoring and early detection of possible deterioration. On the same day as spirometry, patients will report their symptoms and, if any, side-effects on their personal platform. Patients record cough, dyspnea, fatigue, and general complaints on a visual analog scale (VAS) and will also report dyspnea on the Medical Research Council scale (MRC). In case of side-effects, patients can record which side-effects they have and how bothersome they are. When FVC declines ≥10%, or side-effects are burdensome, an email alert will be sent directly to the treating physician, who will contact the patient within 24 h to discuss symptoms and decide whether an extra outpatient clinic visit with pulmonary function measurement is needed. Furthermore, patients will be asked to complete PROMs at every time point before the doctor’s visit.

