### Statistical analyses

The primary analysis will be based on the Intention-to-Treat (ITT) population, defined as all randomized patients who received at least one dose of prednisone or methotrexate. Patients who discontinue treatment prematurely will be analyzed based on the available data. As a sensitivity analysis, a Per Protocol analysis will be performed in all enrolled patients who complete the 24 week treatment regimen without major protocol violations. Change in FVC (% predicted) between baseline and 24 weeks follow-up will be compared between the two groups by using multilevel analysis with the repeated values of FVC as dependent variable and groups, time (defined as categorical variable) and baseline FVC as covariate. To account for the repeated FVC measurements, patient will be included as a random effect. Additionally the interaction terms between the time points and group will be added to assess at which point in time the groups have different average FVC values.

(Generalized) multilevel analyses will also be used to evaluate within and between-group differences in pulmonary function, symptoms, QoL scores, and side-effects over the study period. Between-group differences in mean time to onset of side-effects and time to symptom improvement will be analyzed using Kaplan Meier and log rank test. The Chi square test will be used to evaluate between-group differences in the proportions of patients who discontinue medication, proportion of patients who have FVC improvement and FVC decline, and the proportion of patients who adhere to the treatment schedule. The time to pulmonary improvement, using home spirometry, will be assessed using a linear mixed model, with FVC as dependent variable and time and treatment group as independent variables. Time will be entered as a random effect and will be modelled flexible. Moreover, this model will incorporate the change in curvature of the FVCs temporal trajectory, and thus enable estimation of the time point at which the maximum improvement in lung function is reached. Correlation between lung function, side-effects, QoL scores and symptoms will be analyzed with Pearson Correlation Coefficient. The FVC trajectory over time will be related to the trajectory of QoL scores over time with a linear mixed model. Logistic regression will be used to analyze which clinical or laboratory parameters are associated with disease progression (defined as ≥10% FVC decline) and disease chronicity.

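### In an open-label trial the between-arm harm comparison is framed as side-effects; the tolerability conclusion would be safer on all adverse events, which are already recorded, whatever their judged cause

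*Protocol article*

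**What the plan says.** All references are to the protocol article.

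- **Blinding** (Design and participants): "The PREDMETH study is a prospective, randomized, non-blinded, multi-center, non-inferiority trial".
- **Harm endpoint** (Objectives and endpoints, Table 1, secondary endpoints): "Number, severity and impact of side-effects compared between methotrexate and prednisone".
- **Harm analyses** (Statistical analyses): multilevel models for "within and between-group differences in pulmonary function, symptoms, QoL scores, and side-effects over the study period". For onset: "Between-group differences in mean time to onset of side-effects and time to symptom improvement will be analyzed using Kaplan Meier and log rank test".
- **Patient reporting** (Home monitoring): each week, on the spirometry day, "patients will report their symptoms and, if any, side-effects on their personal platform". Symptoms have their own VAS and MRC entries. For side-effects, "In case of side-effects, patients can record which side-effects they have and how bothersome they are".
- **Adverse events** (Hospital visits): "At follow-up visits all adverse events will be evaluated and recorded". The article mentions adverse events nowhere else: not in Table 1 and not under Statistical analyses.
- **Use of the result**: tolerability is part of the main objective (Objectives and endpoints). The conclusion expected to change practice is that "methotrexate is as effective as prednisone as first-line treatment for sarcoidosis but with fewer side-effects" (Abstract, Discussion).

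**The concern.** The word side-effect carries a causal judgement. Before a complaint counts, someone has to decide that the treatment caused it rather than the sarcoidosis or something unrelated. In this trial the patient and the physician both make that judgement knowing the drug, and it is a different drug in each arm. Two arms with the same burden of complaints can therefore show different numbers of side-effects, and a true difference can be hidden in the same way.

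The article gives reasons to expect room for judgement. Background lists depression both among the symptoms of sarcoidosis and among the harms of corticosteroids. The Abstract and Background describe prednisone as often causing side-effects and methotrexate as appearing to cause fewer, so expectations may differ between arms. Expectations of medication are themselves recorded at baseline.

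At stake is the tolerability half of the intended conclusion. The FVC comparison is not affected.

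**Working it through.** **1. The passages side by side.**

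| Record | Who makes it | Causal judgement implied? | Between-arm comparison stated? |
|---|---|---|---|
| Symptoms (VAS, MRC) | patient, weekly | no | yes |
| Side-effects | patient, weekly in the app; other sources not excluded | yes, by the term | yes (Table 1; Statistical analyses) |
| All adverse events | at follow-up visits | not for entry, as all are recorded | none stated |

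The one broad harm record that does not depend on judged cause is the one without a stated comparison.

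**2. Arm size.** The sample-size section gives SD 10.5, margin 5, one-sided 5% and 80% power:

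n per arm = 2 × (1.645 + 0.842)² × 10.5² / 5² = 54.5, so 55 per arm and 110 in total. With 20% drop-out, 110 / 0.80 = 137.5, so 138, or 69 per arm. This agrees with the article. It is used here only to set the arm size.

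**3. Illustration, on assumed rates.** The article gives no complaint rate and no attribution rate. Let p be the proportion with at least one complaint, equal in both arms, and a₁, a₂ the proportions of those patients who call it a side-effect. The observed proportions are p₁ = p·a₁ and p₂ = p·a₂. For a two-sided 5% test of two proportions with n per arm, the chance of a nominally significant result favouring the arm with lower attribution is

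Φ[(p₁ − p₂ − 1.96·SE₀) / SE₁], with SE₀ = √(2·p̄(1 − p̄)/n), p̄ = (p₁ + p₂)/2, and SE₁ = √((p₁(1 − p₁) + p₂(1 − p₂))/n).

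Example with p = 0.80, a₁ = 0.70, a₂ = 0.50, n = 69:
- p₁ = 0.56, p₂ = 0.40, p̄ = 0.48
- SE₀ = √(0.4992/69) = 0.0851; SE₁ = √(0.4864/69) = 0.0840
- (0.16 − 1.96 × 0.0851)/0.0840 = −0.08; Φ(−0.08) = 0.468

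Results at 69 per arm (55 per arm in brackets):

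| Attribution, arm 1 v arm 2 | p = 60% | p = 80% | p = 90% |
|---|---|---|---|
| equal | 2.5% (2.5%) | 2.5% (2.5%) | 2.5% (2.5%) |
| 70% v 60% | 10.8% (9.4%) | 15.3% (13.1%) | 18.7% (15.7%) |
| 70% v 50% | 31.0% (25.7%) | 46.8% (38.8%) | 56.5% (47.3%) |
| 80% v 50% | 58.4% (49.0%) | 81.3% (71.8%) | 90.5% (82.9%) |

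The calculation is symmetric. Exchanging the arms gives the same figures in favour of the other drug. A comparison of all complaints regardless of cause would show p against p in every cell.

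**4. What the table does not show.** The article does not plan a two-proportion test for side-effects; it plans multilevel models and the log-rank test. One all-or-nothing attribution per patient also simplifies 24 weeks of weekly reporting. The table shows that an attribution gap can matter at this sample size. It does not estimate the bias in this trial.

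**The case against.** **The term may be used loosely.** Side-effects is not defined in the article. Hospital visits moves from adverse events to side-effects in consecutive sentences, and Table 1 does not say that the endpoint comes only from the app. If staff-recorded adverse events already feed it, the point reduces to wording. This stands as a limit. Against it, Home monitoring keeps side-effects apart from symptoms, so the term does some sorting there.

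**Definitions belong in the full protocol.** Correct: the absence of a definition, a causality rule or the app's item wording is no fault in a condensed article. The point is about the comparison that the article does name.

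**Other comparisons cover part of the gap.** Cough, dyspnea, fatigue and general complaints are scored weekly in both arms without attribution, and symptoms and quality of life are compared between groups. Discontinuation and switching are compared too. Weight, blood pressure and laboratory values are collected at visits. A complaint put down to sarcoidosis may therefore still appear somewhere. This offset is real but partial: none of these counts or grades adverse events, and infections, for example, have no scale of their own.

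**Adverse-event recording is also unblinded.** True. Dropping the causal judgement leaves differences in reporting and eliciting.

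**A stronger reading.** A reader might infer that attribution must differ between the arms and must favour methotrexate, so that the hypothesised advantage is built in. The documents do not support this. Background describes known harms for both drugs. The clearest documented overlap, depression, is between sarcoidosis and corticosteroids, and would tend to reduce attribution to prednisone. Headache and malaise are listed for methotrexate but not as symptoms of sarcoidosis. The article also does not describe how the entry screen elicits side-effects.

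**Conclusion.** The point holds as a worthwhile and inexpensive improvement to a secondary comparison. The stated harm endpoint and its analyses rest on a term that implies attribution to a known drug, while adverse events recorded regardless of cause enter no stated comparison. Differential attribution could bias the tolerability result either way. Its direction and size cannot be taken from the article. The range of 10.8% to 90.5% at 69 per arm follows entirely from assumed complaint and attribution rates and from a test that is not planned. The conclusion also assumes that side-effects and adverse events are meant as different things; if they are synonyms, only a clarification is needed. The primary endpoint, the 110 and 138 patients and the non-inferiority conclusion are unaffected.

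**What to change.** - In Table 1 and Statistical analyses, base the between-arm tolerability conclusion on all adverse events recorded after first dose, regardless of judged cause: number, severity and time to first event. Analyse them by randomised arm, since patients may switch to or add the other drug.
- Keep patient-reported side-effects and their impact as a supportive outcome from the patient's perspective, described as attributed without blinding.
- If side-effects in those two places already means all adverse events, state that there. No further change is then needed.

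**Cost.** Wording of one secondary endpoint and its analysis. The visits already record the events, and the sample size stays the same. There are two drawbacks. Disease-related events enter both arms and dilute a true drug difference somewhat, and open-label reporting bias is reduced but not removed.
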